#### Infant measures

At 6 weeks, infant length, weight, and skinfold thickness measurements are performed by trained staff using standardized procedures. BMI *z*-scores are calculated using the WHO Child Growth Standards for age and sex [147]. A *z*-score of > 1 will be used to define at risk for obesity.

#### Demographics and medical/reproductive history

At baseline, participants complete a demographic questionnaire assessing age, race, ethnicity, and weight history (e.g., inter-pregnancy weight changes). Given prior relationships with GDM recurrence [148], extensive pregnancy history information (maternal and neonatal) are collected [149, 150]. At follow-ups, changes in smoking, prescription medications, unsafe dieting practices [117], job status, and participation in other weight loss programs, and changes in medical history are assessed. Pregnancy urine tests are used to assess pregnancy status at quarterly visits until conception. Pregnancy confirmation is documented through clinical ultrasound results.

#### Process measures

Recruitment, eligibility, refusal rates/reasons, and retention rates/reasons are tracked, as well as the number of women who conceive during the trial and the average duration until conception. Intervention acceptability is measured based on participants’ ratings of various aspects of the program, the interventionist, content, and overall impression. To measure intervention fidelity, all intervention sessions are audiotaped, and a randomly selected subset (10%) is coded for content by a trained study staff (not involved in any assessment data collection). Adherence to the intervention is measured via attendance at treatment sessions, number of self-monitoring records returned, and the activity, eating, and behavioral measures. To assess the safety of the intervention, levels of hunger, depressive symptoms, injuries due to physical activity, changes in medical status, and unintended reduction in milk supply (in breastfeeding women) are assessed.

### Participant timeline {13}

Table 3 shows when participants complete the measures in Gestational Diabetes Prevention/Prevención de la Diabetes Gestacional. Bilingual (English/Spanish-speaking) assessors are masked to randomization and conduct all major assessments occurring at baseline, after 16 weeks, at 26 weeks’ gestation, and at 6 weeks postpartum. These assessments occur at the study’s research centers or affiliate locations most proximal to participants. If necessary, assessments are conducted at participants’ homes. After 16 weeks, quarterly brief assessments occur until conception. The brief assessments may be conducted in person or over the phone/video conferencing.

**Table 3 Tab3:** Measures in Gestational Diabetes Prevention/Prevención de la Diabetes Gestacional

	Assessment time point				
	Pre-pregnancy			Pregnancy	Postpartum
	Baseline	4 months	Every 4 months until pregnancy	26 weeks’ gestation	6 weeks
Demographics and medical history	X	X	–	X	X
Weight, height, waist circumference	X	X	X	X	X
Pregnancy test	X	X	X	–	–
**Maternal physiology**					
HbA1c (screening then annually until conception)	X	–	–	–	–
GDM assessment	–	–	–	X	–
Glucose, insulin	X	X	–	X	–
Inflammatory factors	X	X	–	X	–
Lipids	X	X	–	X	–
Blood pressure	X	X	–	X	–
**Lifestyle behaviors**					
Physical activity	X	X	–	X	–
Dietary intake	X	X	–	X	–
Behavioral and psychosocial	X	X	brief	X	–
**Infant weight, length**	–	–	–	–	X
**Maternal/infant complications**	–	–	–	–	X
**Process measures**	–	X	X	–	–

### Sample size {14}

Power calculations assume a 60% GDM recurrence rate in women with overweight or obesity [19, 57, 58]. With a target sample size of 252 participants and assumed ≥ 70% pregnancy rate [151, 152] and 30% lost to follow-up or not pregnant before conception, ≥ 176 pregnant participants (≥ 88 in each group) would provide adequate statistical power (≥ 81.98%) to detect intervention effects on the proportions developing recurrent GDM [83, 153], taking into account estimations of site-specific clustering effects and effect modifiers (i.e., weight status, ethnicity, parity) of GDM recurrence [24, 57]. Under this scenario, the minimum detectable effect size (odds ratio) would be 0.43, and proportions with GDM in educational control and intervention groups respectively would be 60% (*n* = 53/88) and 38% (*n* = 33/88). For secondary aims, 88 pregnancies in each group would yield > 80% power to detect effects equal to or smaller than those reported in prior work testing effects of lifestyle interventions on reductions in glucose, triglycerides, CRP [154], insulin, leptin [155], adiponectin [156], and blood pressure [157], taking into account estimations of site-specific clustering effects and effect modifiers (i.e., weight status, ethnicity, parity) of insulin resistance [158], and CVD risk factors [159, 160]. For secondary aims examining effects of the intervention on prenatal and perinatal complications, the study would have > 80% power to detect moderate effect sizes [161]. For the fourth aim examining the effects of the intervention on pre-pregnancy weight losses and improvements in eating (calories, macronutrient balance, fast food) and activity, 88 participants in each group would yield > 90% power to detect effects reported in prior work testing effects of lifestyle interventions on reductions in weight [157] and behavioral variables [162, 163]. For exploratory mediator analyses, > 80% power is achieved to detect > 21% increase in the mediated odds of GDM per kilogram difference in pre-pregnancy weight loss (equivalent to a mediated slope in a logistic model of > 0.189).

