### Preconception weight loss to reduce gestational diabetes and associated health risks

Observational research suggests that women who experience even modest weight losses (> 10 pounds) [33, 34, 83] or less weight gain [84–86] prior to pregnancy significantly reduce their risk of GDM development compared to women who maintain weight or gain > 10 pounds. Kim et al. [48] estimated that up to half of GDM cases could be prevented by reducing pre-pregnancy obesity. Retrospective data from bariatric surgery populations also suggest that weight loss in women with obesity prior to pregnancy may reduce the risk of GDM and its recurrence [37, 87, 88] and prevent transmission of obesity to children [36]. Other observational research has shown that maternal consumption of healthy food and avoidance of unhealthy foods [89] and engagement in regular physical activity before pregnancy were independently associated with reduced risk of subsequent GDM [89]. Honein et al. [90] estimated that if 10% of women with pre-pregnancy obesity achieved a healthy weight (BMI < 25) before pregnancy, nearly 300 congenial heart defects and 700 fetal deaths per year could be prevented each year.

However, few clinical trials have examined the effects of weight loss during the preconception period on subsequent outcomes [41, 91]. The PREPARE randomized trial [41] tested a phone-based weight loss intervention in 326, non-Hispanic (94%) women with a BMI ≥ 27 and found that, relative to the control group, women in the lifestyle intervention lost more weight prior to conception (3.7 vs. 0.6 kg, respectively). After 24 months, 169 (52%) became pregnant and were included in the analysis. The results indicated that those in the preconception intervention group surprisingly gained more weight during their subsequent pregnancy than those in the control group (13.2 vs. 10.3 kg gain, respectively; *p =* 0.03); there were no significant differences in GDM or other pregnancy outcomes, with the exception of spontaneous pregnancy losses, which were less common in the intervention arm. Participants in the intervention arm had a 10% lower absolute rate of GDM than in the control arm (25% vs. 35%, respectively), but the study had insufficient power to evaluate whether or not a difference of this size was due to chance.

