A trial in Finland [91] randomized women with obesity and/or prior GDM to a nurse-led preconception lifestyle intervention or a control group. Among the 65% who became pregnant during the trial, there were no significant differences by randomized group in the cumulative incidence of GDM, which was 60% (*n* = 39/65) in the intervention group and 54% (*n* = 34/63) in the control group (*p* = 0.49). However, 45% of the participants included in the final analyses received only 1 preconception visit or no intervention at all, and thus, preconception weight change was not analyzed [91]. Other studies have demonstrated feasibility [40] and examined the effects in women with fertility issues [92], and other trials are in progress [93]. Clinical trial data are needed to test whether preconception weight loss can prevent GDM recurrence [35, 46].

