	Hospitalization for depression or psychological problems in the last year
	No show to a scheduled orientation and fail to reschedule

Women must also report chances of having a baby in the next 1–3 years; this is determined based on a response to the question, “On a scale of 0–10, what are the chances you see yourself ever having any more children?” Participants reporting ≥ 1 on this scale and who report plans for pregnancy within the study’s time frame (1–3 years depending on study enrollment year) are considered eligible. Other eligibility criteria include BMI ≥ 25 kg/m^2^, age ≥ 18 years, and English- or Spanish-speaking. Breastfeeding women are eligible to enroll, as moderate weight loss does not appear to adversely affect lactation [110–114]. At study enrollment, participants are encouraged to use medically proven forms of contraception until completion of the initial 16 weeks of intervention, but this is not an eligibility requirement.

Women with type 2 or type 1 diabetes are excluded; the lack of diabetes is confirmed prior to randomization with an HbA1c test (> 6.5%). Women with a family history of diabetes or with impaired glucose tolerance (“prediabetes”; HbA1c of 5.7–6.4%) may be at increased risk of GDM [115] but are included because weight loss could potentially still modify the risk of GDM. Other exclusions include age < 18 years, current pregnancy, tubal ligation, semi-permanent form of birth control with no plans for removal (e.g., hormonal progesterone intrauterine device or hormonal contraceptive implant), relocating in the next 2 years, medications that affect weight/diabetes (e.g., oral corticosteroid and metformin), serious current physical disease (e.g., heart disease, cancer, renal disease) for which physician supervision of diet and exercise prescription is needed, orthopedic problems that limit the ability to exercise [116], problems with drug abuse and/or symptoms of eating disorders [117], history or plans of bariatric surgery, and hospitalization for depression or psychological problems in the past year. Also, women who do not show to orientation visits and fail to reschedule are excluded.

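### The sample-size section pairs 81.98% power and an odds ratio of 0.43 with proportions that do not match it, and leaves almost no room for pregnancies without a GDM outcome

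*Protocol article*

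**What the plan says.** All the figures stand in the protocol article, Sample size {14}.

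- Control rate: "Power calculations assume a 60% GDM recurrence rate in women with overweight or obesity".
- From 252 randomized to the number analysed: "assumed ≥ 70% pregnancy rate [151, 152] and 30% lost to follow-up or not pregnant before conception, ≥ 176 pregnant participants".
- Power: "≥ 88 in each group) would provide adequate statistical power (≥ 81.98%) to detect intervention effects".
- Effect: "the minimum detectable effect size (odds ratio) would be 0.43", and the proportions in the control and intervention groups "respectively would be 60% (*n* = 53/88) and 38% (*n* = 33/88").

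The section says that site clustering and effect modifiers were taken into account, but gives no figure for either.

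Elsewhere, Outcomes {12} places GDM testing at 24–28 weeks' gestation. The paragraph on HbA1c tests counts earlier clinical diagnoses. Section {20c} puts all confirmed pregnancies in the primary analysis, uses provider records when the study's glucose tolerance test is missing, and allows multiple imputation. Section {21a} has the safety officers review miscarriages.

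**The concern.** Two things in this one section do not fit together.

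First, the detectable effect is given twice, as an odds ratio and as a pair of proportions, and the two are different effects. The single power figure cannot belong equally to both.

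Second, one 30% is said to cover both women who do not conceive and women who are lost. A 70% pregnancy rate already uses all of it. The resulting 176 are pregnant women, yet the primary outcome is normally established months after conception. Nothing is set aside for miscarriage or for loss between conception and testing.

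At stake is how the primary result will be read. A null finding would be taken as coming from a trial with about 82% power for a stated effect, so both the effect and the number of outcomes behind that figure should be right.

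**Working it through.** **Inputs (Sample size {14}; 1:1 allocation from Trial design {8}).** 252 randomized; at least 70% pregnant; 88 per group; control 60%; intervention 38%; odds ratio 0.43; power at least 81.98%. The article gives no alpha or test, so two-sided 5% is assumed. That choice fits the stated figure; a one-sided 5% test at 60% vs 38% would give 90.4%.

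**1. Reproduce the stated power.** Pooled two-proportion test:

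power = Φ{[|p1 − p2| − 1.96·√(2p̄(1 − p̄)/n)] / √[(p1(1 − p1) + p2(1 − p2))/n]}

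With p1 = 0.60, p2 = 0.38, p̄ = 0.49, n = 88: (0.22 − 1.96 × 0.0754)/0.0735 = 0.983, and Φ(0.983) = 83.7%. Other two-sided versions give 82.5% (log odds ratio), 81.8% (Fisher), 84.9% (unpooled) and 79.6% (continuity-corrected). The stated 81.98% is thus reproduced, to within 2 points by the pooled test, for 60% vs 38% with 88 outcomes per group.

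**2. Check the odds ratio.** OR = [p2/(1 − p2)]/[p1/(1 − p1)].

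- 60% vs 38%: (0.38/0.62)/(0.60/0.40) = 0.409.
- 53/88 vs 33/88: (33/55)/(53/35) = 0.396.
- OR 0.43 from 60%: odds 0.43 × 1.5 = 0.645, so p2 = 0.645/1.645 = 39.2%, or about 34.5 of 88.

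Rounding does not close the gap with control at 60%: even 38.5% gives 0.417. Only 59.5% vs 38.5%, both roundings stretched to the limit, gives (0.385/0.615)/(0.595/0.405) = 0.426, and the printed counts (60.2% and 37.5%) rule that out.

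**3. Power at the stated odds ratio.** With p2 = 0.392, p̄ = 0.496, n = 88: (0.2079 − 1.96 × 0.0754)/0.0737 = 0.816, and Φ(0.816) = 79.3%. Other versions: 78.2% (log odds ratio), 77.1% (Fisher), 80.5% (unpooled), 80.4% (exact chi-square), 74.6% (continuity-corrected). None of these two-sided tests reaches 81.98%; the pooled test would need 95 per group.

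**4. The attrition step.** 252 × 0.70 = 176.4. The pregnancy rate alone produces 176, so the allowance for other loss is 0%. The text is coherent only if more than 70% conceive, and 176 takes no credit for that.

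**5. Sensitivity to outcomes missing among pregnant women.** The documents give no such rate; those below are assumptions. Pooled test, two-sided 5%:

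| Pregnant | Without outcome | Outcomes | Power, 60% vs 38% | Power, OR 0.43 |
|---|---|---|---|---|
| 70% | 0% | 176 | 83.7% | 79.3% |
| 70% | 5% | 167 | 81.8% | 77.2% |
| 70% | 10% | 158 | 79.7% | 74.9% |
| 70% | 15% | 150 | 77.3% | 72.4% |
| 70% | 20% | 141 | 74.8% | 69.8% |
| 65% | 0% | 164 | 81.0% | 76.3% |

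The 65% row uses the pregnancy rate of the Finnish trial described in the introduction ("Among the 65% who became pregnant during the trial"). At 60% vs 38%, power falls below 81.98% once about 4.5% of the 176 (about 8 women) have no outcome.

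**The case against.** **The power figure is right for the proportions given.** This stands. At 176 outcomes and 60% vs 38%, the pooled test gives 83.7%. No arithmetic error in the power has been shown for those inputs.

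**The 0.43 may be the detectable odds ratio at 80% power.** At 88 per group and 60% control, the pooled test detects 0.427 at 80% power and 0.417 at 81.98%. This is a possible origin, but the text does not say so and places 0.43, 81.98% and 38% in one scenario.

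**Stratification and covariate adjustment may add power.** Randomization is within site and the model adjusts for prognostic covariates, so a cluster-trial inflation does not automatically apply and some gain is possible. At OR 0.43 it would have to be worth about 8% in sample size (95/88 = 1.08). No such gain is stated, and it would not turn 0.43 into 38%: a covariate-conditional odds ratio would lie further from 1 than 0.409, not nearer.

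**Fallbacks recover untested women.** Provider records and early diagnoses do reduce missing outcomes. They do not supply a result for a woman who miscarries undiagnosed or is lost after conception, and imputation does not restore the missing information.

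**A stronger reading goes too far.** A reader might infer that the design really has only 65–77% power, since one cited preconception trial reports "After 24 months, 169 (52%) became pregnant and were included in the analysis" and eligibility admits "Participants reporting ≥ 1 on this scale" of 0–10. The documents do not support this. Every figure in that range needs an assumed 15% loss, a 52% pregnancy rate, or both. The 52% comes from women with BMI of at least 27 over 24 months, not women selected for prior GDM; the introduction's other trial, which enrolled women with obesity and/or prior GDM, reached 65%, giving 81.0%. The same eligibility sentence also requires pregnancy plans within the study's time frame, as does Table 1. The sources behind the 70% cannot be examined here.

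**Conclusion.** The concern holds in a limited form. The stated power, odds ratio and proportions are not mutually consistent: 60% vs 38% is OR 0.41 with about 82–84% power at 88 per group, while OR 0.43 is 60% vs 39.2% with about 79% (77–80.5% depending on the test).

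Separately, the 30% is fully spent on non-pregnancy, and 176 counts pregnancies rather than outcomes. The 81.98% is therefore conditional on the 60% vs 38% effect and on practically complete outcome data. With assumed outcome loss of 5–20% among pregnant women, power is about 82% down to 75%.

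These figures rest on two-sided 5%, a 60% control rate, equal groups, a 70% pregnancy rate and no quantified gain or loss from clustering or covariates. The documents do not show that the stated power will fail to be reached, because they give no rate of post-conception loss.

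**What to change.** Restate Sample size {14} as follows.

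1. Reconcile the effect: either OR 0.41 with 60% vs 38%, or OR 0.43 with 60% vs 39% and about 79% power. Align the counts and name the test and alpha behind the figure.
2. Give the pregnancy rate and the loss after conception (pregnancy loss before testing, loss to follow-up) as separate factors.
3. Base the calculation on women with an assessable GDM outcome.
4. Report power and detectable odds ratio over a plausible range of outcomes. For 141 to 176 outcomes, power at 60% vs 38% runs from about 75% to 84%, and the odds ratio detectable at 81.98% power from about 0.38 to 0.42 (pooled test, two-sided 5%).

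The cost is text only; no extra enrolment is proposed. The downside is that the stated power becomes slightly less favourable.

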### Recruitment {15}

To reach the target sample size of 252, a 3-year recruitment time frame is proposed. Both sites recruit participants through direct and indirect methods and via administrative databases. As described in Table 4 direct recruitment methods include clinic staff and research assistants at the recruitment clinics providing information about the study at the time of prenatal or postnatal visits for patients with GDM or prior GDM. Indirect methods include presentations in healthcare settings that interact with mothers (e.g., Ob/Gyn, pediatrician, WIC offices). Administrative databases are also used to identify and offer the program to women with a history of GDM who might not regularly engage with the targeted healthcare settings after having a baby.

**Table 4 Tab4:** Recruitment methods for reaching preconception women with prior gestational diabetes mellitus

**Direct to patient**	
In-person recruitment by clinic or study staff during pregnancy or 6 weeks postpartum visits	
Brochures and posters in clinics and waiting rooms	
Social media (Facebook, Instagram) posts, videos, and advertisements	
Traditional media (television, radio, flyers)	
Online forums posts	
**Indirect through women’s health providers (e.g., Ob/Gyn, WIC)**	
Presentation and clinic meetings	
1-page fact sheets	
Study write-up for newsletters directed at providers	
**Administrative databases**	
Hospital patient databases	
Community health center patient database	
Review of research center database	
Research match	

## Assignment of interventions: allocation

### Sequence generation {16a}

Eligible participants are randomized in a 1:1 ratio into the intervention or control group based on a computer-generated (R 4.0.4 for Windows) random sequence. Randomization is stratified by site, pre-diabetes status (HbA1c < 5.7 vs. ≥ 5.7), and prior method of GDM diagnosis (one-step, 2 h test vs. other methods) to ensure a balance of the two interventions within each stratum.

### Concealment mechanism {16b}

The allocation sequence is implemented via sequentially numbered, opaque, sealed envelopes that are concealed until the interventions are assigned to a participant.

### Implementation {16c}

The study statistician generates the allocation sequence. Study interventionists enroll participants and, based on opening the envelope, assign participants to interventions.

## Assignment of interventions: blinding

### Who will be blinded {17a}

Research assistants are masked to randomization, and participants do not know the assigned group until after baseline measures are completed.

### Procedure for unblinding if needed {17b}

Unmasking is not needed.

## Data collection and management

### Plans for assessment and collection of outcomes {18a}

All staff involved in data collection must demonstrate competence in administering all measures. The research assistants collecting the data are masked to the participants’ intervention assignment. The research assistants review all assessment data for accuracy and completion. Participants are immediately re-contacted to provide missing data or to clarify responses. Loss to follow-up and missing and incomplete data are monitored closely to solve potential issues of missing data before there is a substantial impact on the results.

### Plans to promote participant retention and complete follow-up {18b}

To minimize loss to follow-up, at each data collection visit, participants are scheduled by phone, sent written reminders, and called the day before. Missed visits are rescheduled and followed up. Costs for transportation and childcare are provided, or alternatively, home visits are arranged for participants with repeatedly missed assessments. Honoraria are provided to promote retention: $25 for visits at study entry, 16 weeks, and 6 weeks postpartum visit; $15 per quarterly visit until conception; and $50 for the primary outcome assessment at 26 weeks’ gestation. As a retention tool, women in both groups also receive quarterly newsletters with basic information about preconception health and wellness.

### Data management {19}

Research Electronic Data Capture (REDCap) is used for storing study outcome measurement data. A customized internal study tracking system is used to track enrollment and scheduling of visits. Both systems require a login identification and password in order to gain access to the data. Range checks are built into the data collection procedures to alert staff to data that should be clarified. Error checking and preliminary analyses of all data are done to ensure accuracy. Electronic data files are backed up; a copy is stored offsite at both locations to protect against loss or damage. The destruction of any paper files will be at least 7 years from the termination of the study and will be authorized by the PI.

